### Outcome measures

The efficacy of the Cognitive Gym protocol will be assessed with (1) pre- and post-intervention cognitive testing administered *via* CogMission online platform (Wells et al., 2021; Kucina et al., 2022), (2) athletes’ self-ratings of their typical cognitive performance over the preceding 3-week period, and (3) coach ratings of athletes’ performance in their sport-specific training to evaluate the all-important far transfer.

#### CogMission platform

The CogMission online testing platform (Wells et al., 2021; Kucina et al., 2022) delivers a testing protocol based on a gamified dynamic scenario containing trials made up of the following three tasks, all requiring a binary response by pressing either the Left (z) or Right (/) key on the keyboard:

Working memory basic task. Participants are asked to remember which of three doors was highlighted two trials ago and what symbol (0/×/+) is present on the door, then use that information to decide if the door highlighted on the current trial matches.Stop-signal task. This is a classical task used to measure response inhibition (Matzke et al., 2018). An arrow appears on the highlighted door and the participant notes which direction it points. If a red outline appears around the door after the arrow appears (25% of trials) the participant must withhold their response. The stop-signal delay (from the onset of the arrow to the red frame over the door) is adjusted over trials to ensure that stopping is successful on approximately 50% of trials.Selective attention task. The task measures the ability to control interference from irrelevant spatial and verbal information using Stroop (MacLeod, 1991) and Simon tasks (Hommel, 2011), and information from irrelevant spatial locations using a Flanker task (Eriksen, 1995). The door opens, the room behind is shown, a cue at the top of the screen indicates the side where opposition is hiding, and the participant must press the corresponding button. Cues can be the direction of a central arrow (surrounded by flanking arrows: left = <<<<< or > > <>>, right = >>>> > or > > <>>) or the color (e.g., left = blue, right = orange) of a rectangle or word (“BLUE” or “ORANGE”). Two such decisions are made in sequence on each trial, sometimes with the same type of cue and sometimes with different cues. This allows measurement of cognitive flexibility in terms of updating goals using a task switching paradigm (Monsell, 2003). That is, on each trial participants perform two conflict task trials in a row. When the two tasks are the same, the second trial does not require updating the goals established by the first (a “repeat” trial). If the two tasks differ the second trial requires updating of goals (a “switch” trial). Slower response times on switch trials relative to repeat trials indicate reduced flexibility.

An important feature of this protocol is that it combines the Stroop task with Simon task. Stimuli (the words BLUE or ORANGE presented in either a blue or orange font) appear on either the left or right of the screen. Participants respond to the color of the word (e.g., pressing an “orange” key on the left or a “blue” key on the right). Stroop interference is produced when, for example the word BLUE is presented in orange. Simon interference is produced when the word appears on the opposite side to the key indicating the color of the word (e.g., pressing the right key for a blue word that is presented on the left). This combination has been shown effective in reducing the testing time and improving the reliability of the resulting individual differences measures (Wells et al., 2021; Kucina et al., 2022).

Participants initially perform a short (20-min) self-paced tutorial to familiarize themselves with each of the tasks. Participants then perform 16 sets of 12-trial “games” taking self-paced rest breaks between each game. To maintain motivation and engagement, points are awarded for correct choices with bonuses for fast responding. The resulting measures include working memory, response inhibition, and cognitive flexibility.

#### Athlete self-ratings

Cognitive Fitness self-assessment, a set of 20 self-rating scales assessing the individual’s perception of their typical cognitive performance over the preceding 3-week period. Details are in Supplementary material S1.

#### Coach ratings

Coach assessment of “far transfer”: to ascertain the extent of training gains transfer to the sporting contexts, athletes will be rated by their coaches. Coach ratings assess the athlete’s attributes such as composure in competition (e.g., 1 = cool, 2 = calm, 3 = worried, 4 = flustered) and adaptability (e.g., 1 = rigid; 2 = gets stuck; 3 = flexible; and 4 = fully adaptive). More details are in Supplementary material S1.

### Planned analyses

It is expected that, with practice, participants will improve their performance scores on the respective drills. These changes will be monitored and evaluated throughout the intervention. A single blind strategy will be utilized, with researchers administering pre- and post-assessments having no access to the information on which crossover group the participants belong to (training-first or waiting-first).

Improved scores on the drills, however, is no guarantee that participants have learned skills that transfer to similar cognitive tasks (i.e., near transfer), such as the working memory, response inhibition, and cognitive flexibility tasks included in the CogMission battery. Near transfer effects will be evaluated by estimating training gains defined as differences between each CogMission measure at baseline and at the end of the Cognitive Gym training.

Repeated measures ANOVA and mixed linear modelling will be used to estimate effect sizes. Effect size of *d =* 0.4 on training-induced change is considered meaningful and practically important, based on a meta-analysis of randomized controlled trials examining the effects of similar programs on stress (Dhir et al., 2021). This effect size corresponds to *f =* 0.25 for ANOVA power calculations. To reliably detect effects of this size, with two groups and three repeat measurements in our design, G*Power calculations return a minimal sample size of 28 participants (Faul et al., 2009). Allowing for sample attrition and the uncertainty associated with extrapolating power calculations for mixed linear modelling, this study will aim to recruit 60 participants.

Far transfer effects will be evaluated through the coach and athlete ratings. Despite some well-known limitations of self-reports, they have advantages such as easy interpretability, information richness, and practicality (Paulhus and Vazire, 2009). Similar ANOVA and mixed linear modelling will be applied to assess training gains on these measures. Evidence of both near and far transfer effects will address the frequently-voiced objections that gamification techniques lead to improved performance in the games themselves but not in the broader skills they are meant to develop.

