### Study design

A cross-over design was chosen for this study as it improves statistical power by making each participant a baseline for themselves. It is also driven by the need to achieve sufficient buy-in from the participants and their coaches—the groups known for their dislike for passive control designs where participants in control conditions can miss out on the potentially beneficial intervention.

In our cross-over design participants will be randomly assigned to either a “training-first” or “waiting first” group. All participants will complete baseline assessment using methods (described in “Outcome measures”) at the start of Week1 (Time 1), then repeat it at the start of Week 4 (Time 2) and at the completion of Week 6 (Time 3). A single blind strategy will be utilized, with researchers administering pre- and post-assessments having no access to the information on which group the participants belong to (training-first or waiting-first).

Following Time 1 assessment, the “training-first” group will commence the three-week training program described in Section 3.3 above, spending 30 min a day practicing the drills delivered through the Cognitive Gym app. The “waiting first” group will have no engagement with the Cognitive Gym app for the first 3 weeks but will have access to the companion website for the designated 30 min daily. They will commence their three-week training with the app immediately after Time 2 assessment. Access to the app will cease for the “training-first” group after Time 2. As a result, each participant will go through 3 weeks of Cognitive Gym app-supported training and 3 weeks waiting, with half of them randomly assigned to training first and then waiting, and the other half—to a reverse order. Coach ratings of athlete progress will be examined in the evaluation, so their consent to participate will also be sought.

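### The sample-size paragraph converts d = 0.4 to f = 0.25, but for two means it is f = 0.20; under the usual settings that reproduce 28, the minimum becomes 42

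*Protocol article*

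**What the plan says.** The whole calculation is in the Planned analyses section of the protocol article.

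- An effect of d = 0.4 "on training-induced change is considered meaningful and practically important".
- The conversion: "This effect size corresponds to *f =* 0.25 for ANOVA power calculations".
- The design entered: "with two groups and three repeat measurements in our design".
- The result: "G*Power calculations return a minimal sample size of 28 participants".
- The target: "this study will aim to recruit 60 participants". The reason given for going above 28 is: "Allowing for sample attrition and the uncertainty associated with extrapolating power calculations for mixed linear modelling". No attrition rate is given.
- The analysis: "Repeated measures ANOVA and mixed linear modelling will be used to estimate effect sizes".

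The Participants section refers the reader to this calculation as the basis for 60. The Study design section splits the sample equally between the two sequences ("with half of them randomly assigned to training first and then waiting"). Alpha, power, the correlation among repeated measurements and the sphericity correction are not stated.

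**The concern.** The paragraph starts from an effect the authors call meaningful, converts it to another scale, and reads a sample size off the converted value. If the conversion is wrong, the sample size answers a different question. The usual two-mean relation gives f = 0.20, whereas 0.25 corresponds to an effect a quarter larger (0.5 against 0.4).

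Two things depend on this. One is the claim that 28 participants are enough to detect the named effect reliably; a reader who accepted 28 completers as adequate would be relying on it. The other is the case for 60, which the article presents as 28 plus an allowance. If the starting number is too low, the allowance is smaller than it looks.

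**Working it through.** **Inputs.** From the article: d = 0.4, f = 0.25, 2 groups, m = 3 measurements, minimum N = 28, target 60, equal allocation. Assumed because the article does not give them: alpha 0.05, power 0.80, correlation rho = 0.5, sphericity (epsilon = 1).

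**Step 1: the conversion.** For two means, f = d/2.
- d = 0.4 gives f = 0.4/2 = 0.20.
- f = 0.25 corresponds to d = 2 × 0.25 = 0.5.

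This step needs none of the assumed settings.

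**Step 2: reproduce 28.** For the within-subject factor or the group-by-time interaction, the noncentrality is lambda = f² × N × m/(1 − rho), with df1 = m − 1 = 2 and df2 = (N − 2)(m − 1). At f = 0.25 and N = 28:
- lambda = 0.0625 × 28 × 3/0.5 = 10.5; df = 2 and 52; power = 0.812.
- N = 28 is the smallest total that reaches 0.80, which matches the printed figure.

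The between-groups test needs 86 at the same f and correlation, so it is not the source of 28.

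**Step 3: change only f to 0.20.**
- N = 28: lambda = 0.04 × 28 × 3/0.5 = 6.72; power = 0.609.
- N = 42: lambda = 0.04 × 42 × 3/0.5 = 10.08; df = 2 and 80; power = 0.803. This is the smallest N that reaches 0.80.
- N = 60: lambda = 14.4; power = 0.929.

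**Step 4: vary the assumed correlation (80% power).**

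| rho | N at f = 0.25 | N at f = 0.20 |
|---|---|---|
| 0.3 | 38 | 58 |
| 0.5 | 28 | 42 |
| 0.7 | 18 | 26 |

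Another setting that gives 28 at f = 0.25 is rho = 0.7 with power 0.95. It also gives 42 at f = 0.20.

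**Step 5: look for a reading that rescues 0.25.**
- Three measurement means spanning 0.4 SD give f between 0.4 × √(1/6) = 0.163 and 0.4 × √8/6 = 0.189. Both are further from 0.25.
- If d = 0.4 is standardized by the SD of the change score, f = 0.2 × √(2(1 − rho)). This equals 0.25 only at rho ≈ 0.22, and at that correlation the required N is 42, not 28.

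No reading tried supports both 0.25 and 28.

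**Step 6: the room up to 60.** 60 − 28 = 32 participants; 60 − 42 = 18, which is 30% of 60.

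**The case against.** The strongest reply is that the operative number is 60, not 28, and 60 holds up. At f = 0.20 and correlation 0.5 it gives power of about 0.93; if 48 remain (a 20% loss) power is about 0.86; at correlation 0.3 all 60 give about 0.82. The study is presented as proof of concept, and no recruitment or design decision changes. This stands, and it limits the severity.

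Second, 42 is conditional. It rests on four settings the article does not print. The number 28 is not even unique to f = 0.25: at f = 0.20 with 80% power it also comes out at a correlation of 0.68 or 0.69. This stands too. Since the article says it used 0.25, that route is probably not the one taken, and it would leave the printed conversion wrong in any case.

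Third, f = d/2 is a two-mean formula, while the design has two groups, three measurements and a crossover. The appropriate f depends on the pattern of means and the test. The three-level patterns above (0.163 to 0.189) would need 62 to 48 participants. If the groups differed by d at Time 2 alone, the interaction f would be about 0.094. This does not rescue 0.25, since all these values lie below it. It does mean that 0.20 should not simply be substituted without naming the test.

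A reader might infer that 60 is too few, or that an attrition allowance printed in the plan is wrong. The documents support neither. They do not fix a pattern of means that would make 60 inadequate, and they give no attrition rate. The gap between 28 and 60 is meant to cover mixed-model uncertainty as well as dropout, so it cannot be read as an attrition percentage alone.

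**Conclusion.** The point holds as an error in a printed conversion, with a consequence for the minimum sample size that depends on unstated settings. That d = 0.4 does not correspond to f = 0.25 needs only the two-mean relation. That the minimum becomes 42 instead of 28 (half as many again), and that 28 gives about 61% power, assumes alpha 0.05, power 0.80, correlation 0.5, sphericity and f = 0.20. Across correlations of 0.7 to 0.3 the requirement at f = 0.20 runs from 26 to 58.

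Under the settings that reproduce it, 28 does not support the effect the plan calls meaningful, and the allowance built into 60 is a little over half of what the text implies. The target of 60 is not shown to be inadequate. The text is wrong as written and should be fixed, but the error does not threaten the trial.

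**What to change.** In Planned analyses, do one of the following.

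1. Replace f = 0.25 by f = 0.20, or by the f derived for the specific within-subject or interaction test that will be used. Rerun the G*Power calculation and state alpha, power, correlation and sphericity beside the result (42 under the settings above). Then justify 60 against that number, saying how much of the difference is for attrition and how much for the mixed-model extrapolation.
2. Keep f = 0.25 and 28, and state that the detectable effect is d = 0.5. The text should then acknowledge that the minimum is not set for the effect of 0.4 named as meaningful.

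The cost is a few sentences and one rerun of the calculation. With f = 0.20 and correlation 0.5 the recruitment target of 60 can stay. If the authors derive a smaller f for their chosen test, they should check 60 against it.

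### d = 0.4 does not correspond to f = 0.25 in this two-group, three-time design, so the claim that 28 participants reliably detect it is wrong; what 60 can detect depends on unstated assumptions

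*Protocol article*

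**What the plan says.** All the sample-size figures stand in one paragraph of Planned analyses.

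- The target is an effect of d = "0.4 on training-induced change is considered meaningful and practically important", a benchmark taken from a meta-analysis of randomised trials "examining the effects of similar programs on stress".
- This d is said to correspond to f = "0.25 for ANOVA power calculations".
- "To reliably detect effects of this size", "with two groups and three repeat measurements in our design", the result is that "G*Power calculations return a minimal sample size of 28 participants".
- To cover attrition and the uncertainty of carrying the calculation over to mixed models, "this study will aim to recruit 60 participants".

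The same section defines near-transfer gain as the change in each CogMission measure from baseline to the end of training, and plans repeated measures ANOVA and mixed linear models.

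Study design supplies the structure. Participants are randomised half and half to training-first or waiting-first and assessed at Times 1, 2 and 3. The waiting-first group starts the app straight after Time 2, when the training-first group loses access. As a result "each participant will go through 3 weeks of Cognitive Gym app-supported training and 3 weeks waiting".

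The article does not name the G*Power test, alpha, power, the correlation between repeated measures, the attrition rate, or whether gains are expected to persist after training stops.

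**The concern.** The f entered in a repeated-measures power calculation has to be the f that the target effect produces in the design at hand. Here two things go wrong. The conversion from d to f is off even for a simple two-group comparison. Beyond that, the design spreads the training effect thinly: the groups are equal at Time 1 by randomisation, only one is trained at Time 2, and both have been trained by Time 3. If gains last, the groups differ at one of three time points, and the group-by-time effect is much smaller than the Time 2 difference suggests.

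At stake is a detectability claim for evidence on near and far transfer that is meant to inform how the program evolves. Someone reading an inconclusive result against the claim would credit the study with more sensitivity to d = 0.4 than its randomised comparison may have.

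**Working it through.** **Inputs.** From the article: d = 0.4, f = 0.25, k = 2 groups, m = 3 times, 28 and 60 participants, 1:1 allocation. Assumed, because not stated: alpha 0.05, power 0.80, correlation r = 0.5, sphericity. These assumptions are the ones that return 28.

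**1. Reproduce 28.** For the interaction, lambda = f² × N × m / (1 − r), with df1 = (k − 1)(m − 1) = 2 and df2 = (N − k)(m − 1).

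- f = 0.25, N = 28: lambda = 0.0625 × 28 × 3 / 0.5 = 10.5, df = 2 and 52, power 0.81. N = 28 is reproduced.
- The within-factor (time) test has the same lambda and df here and also gives 28. The between-factor test gives 86.

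**2. Correct only the conversion.** For two equal groups f = d/2 = 0.20; f = 0.25 would be d = 0.5. Then N = 42 for 80% power, and power at 28 is 0.61 (lambda = 0.04 × 28 × 3 / 0.5 = 6.72).

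**3. The f this design produces at d = 0.4.** Take half the group difference at each time, subtract the mean of the three values, and take the root mean square.

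- Gains retained: differences 0, 0.4, 0; halves 0, 0.2, 0; centred −0.067, 0.133, −0.067; f = 0.094.
- Gains fully lost: differences 0, 0.4, −0.4; halves 0, 0.2, −0.2, already centred; f = √(0.08/3) = 0.163.

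Neither reaches 0.25 or 0.20. An interaction of 0.25 would need d = 0.4 × 0.25/0.0943 = 1.06 (retained) or 0.4 × 0.25/0.1633 = 0.61 (lost).

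**4. Power for d = 0.4.** N counts completers; d is in raw-score SD units except for the paired test.

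| Test | r | N = 28 | N = 60 | N for 80% |
|---|---|---|---|---|
| Interaction (2 df), retained | 0.5 | 17% | 33% | 184 |
| Interaction (2 df), retained | 0.7 | 26% | 52% | 110 |
| Interaction (2 df), lost | 0.5 | 44% | 79% | 62 |
| Interaction (2 df), lost | 0.7 | 66% | 95% | 38 |
| Time 2 adjusted for Time 1 | 0.5 | 22% | 42% | 150 |
| Time 2 adjusted for Time 1 | 0.7 | 30% | 57% | 104 |
| Paired pre-post, d in change-score SDs | – | 53% | 86% | 52 |

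The interaction rows at r = 0.5 were checked with 20,000 simulated trials: 0.175 and 0.336 (retained), 0.441 and 0.791 (lost). The adjusted rows use a two-sample t test with effect 0.4/√(1 − r²), that is 0.462 and 0.560.

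**5. Units of d.** If d is scaled by the SD of change, as the article's wording suggests, the raw-score effect is 0.4 × √(2(1 − r)). The factor (1 − r) then cancels in lambda, and the interaction has 17% and 33% power (retained) at 28 and 60 whatever the correlation.

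**6. Attrition.** No rate is given. If 20% is assumed, 48 complete, and the retained-gain interaction falls from 33% to 27% at r = 0.5.

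**7. What 60 completers can detect.** An unadjusted two-sample t test with 30 per group has 80% power at a standardised difference of 0.736. Multiplying by √(1 − r²) gives 0.736 × 0.866 = 0.64 at r = 0.5 and 0.736 × 0.714 = 0.53 at r = 0.7.

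**The case against.** The case for the plan is strongest on the 60, which is the number actually to be recruited.

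- **The article never says that the interaction was tested.** True. The time effect also returns 28. But a time effect mixes training with retest practice on a repeated battery and makes no use of the randomised waiting group.
- **On the article's own definition of gain, 60 is enough.** A pre-post paired test with 60 completers has 86% power. This stands, with two limits: the comparison is uncontrolled, and 28 gives only 53% even here.
- **Mixed models over three times do better than the omnibus test.** Also true. A one-degree-of-freedom contrast using all three times, with the gain pattern known, has 46% (r = 0.5) or 65% (r = 0.7) power at 60 with gains retained, and 86% or 98% with gains lost.
- **A higher correlation would help.** With d in raw-score SD units and gains retained, the interaction test at 60 reaches 83% at r = 0.85. With gains fully lost, 28 would reach 84% at r = 0.8. But such a correlation was not behind the calculation: f = 0.25 with r = 0.8 would have returned 12, not 28.

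Three stronger readings are tempting, and the documents do not support them. A reader might infer that 60 is inadequate outright; that depends on contrast, retention and correlation, and under some combinations 60 suffices. A reader might reduce the matter to a one-in-three chance of detection; that figure belongs to the 2-df interaction or the Time 2 change-score test with gains retained at r = 0.5, and baseline adjustment already raises it to 42%. A reader might say that the benchmark concerns stress, which the trial does not measure; the self-rating and coach items are in Supplementary material S1, which is not shown, so this cannot be established.

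**Conclusion.** The sample-size statement is wrong as written. The arithmetic of 28 is sound for f = 0.25, but d = 0.4 is f = 0.20 by the two-group conversion (42 participants) and 0.094 to 0.163 as a group-by-time effect here. At the correlation that reproduces 28, power at 28 is 17% to 53% across the tests considered, so reliable detection is not supported.

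For 60 the conclusion is conditional. The randomised comparison is well short of 80% if gains are retained and the correlation is 0.5 to 0.7, is near 80% for the interaction if gains vanish and the correlation is 0.5, and the uncontrolled pre-post test exceeds 80%. Alpha 0.05, 80% power, sphericity and the correlations are assumptions; the article gives none of them. All the figures for 60 assume no attrition, which would lower every one.

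**What to change.** Rewrite the paragraph in Planned analyses:

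1. Delete the claim that 28 participants reliably detect d = 0.4, and correct the conversion from d to f.
2. Name the randomised contrast that carries the training effect. It can be training-first against waiting-first at Time 2 adjusted for Time 1, or the equivalent treatment contrast in the three-time mixed model, which keeps the Time 3 data and the crossover rationale.
3. State alpha, power, the units of d, and the assumed correlation, retention of gains and attrition.
4. Restate what 60 can detect. For the baseline-adjusted Time 2 contrast with 60 completers, that is d of about 0.64 (correlation 0.5) to 0.53 (correlation 0.7) at 80% power, with 42% to 57% power for d = 0.4. If the mixed-model contrast is chosen, give the figures for that contrast.

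The cost is one rewritten paragraph and a less favourable stated power. The recruitment target and the conduct of the study do not change.
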